#### Participants timeline

Participants are included while still on the inpatient ward or at latest 3 weeks after initiating treatment at the IOS and are followed for 4 weeks (see Spirit flow diagram in Fig. 3).

**Fig. 3 Fig3:**
[figure not shown]
SPIRIT flow chart of study procedures

#### Sample size

Sample size calculations were done using the SAS 9.4 software.

The sample size for the primary outcome was calculated from an expected HAM-D_17_ mean score of 18 at baseline, a decrease to a score of 13 in the *Standard group* arm and to 10 in the *CRF group,* an expected pooled standard deviation of 6, an alpha level of 0.05 and a power of 0.80: a total of 128 participants is needed.

The sample size for the secondary outcome was calculated from an expected MDI mean score of 27 at baseline, a decrease to 22 in the *Standard group* and to 16 in the *CRF group*, with an expected pooled standard deviation of 12, an alpha level of 0.05 and a power of 0.80: a total of 128 participants will be needed.

The sample size for the tertiary outcome was calculated from an expected PAD of 5 h in the *CRT group* at baseline (a phase delay) normalizing to 6 h at endpoint, an unchanged PAD of 6 h in the *Standard group*, a PAD standard deviation of 80 min, an alpha level of 0.05 and power of 0.80: a total of 58 patients will be needed. We will collect saliva samples in 58 consecutive patients from participant randomization number 72.

#### Recruitment

When the IOS receive a referral, the attending physician will pass on information from the patient’s case file to the investigator, regarding age, dementia, psychotic episodes, and bipolar illness. If no exclusion criteria are present, investigators will contact the referring ward.

## Methods (assignment of interventions)

### Allocation

The randomization list was created from a computer randomization solution (http://www.randomization.com), by a person without any other connection to the trial. In all, 152 randomization numbers have been created allocating into either the *CRT group* or the *Standard group*, with no stratification factors. The randomization list is only accessible to the investigator responsible for randomization. The randomization sequence has been transferred to code-letters, stored in opaque envelopes in a locked cabinet. Block size is blinded for investigators. Primary investigator will enroll and assign participants to interventions. The patient will be allocated to the next study number and given an opaque allocation envelope containing information of trial group allocation: *Standard group* or *CRT group*.

### Blinding

The rater performing the Hamilton interview is blinded to treatment allocation and has no other association with the study. We do not consider it necessary in any circumstances to reveal a participant’s allocated intervention during the trial.

### Data management

Data from the MDB application is exported from the website after each completed patient, as an excel file. All data files are stored on a secure logged server approved by the Danish Data Protection Agency. Paper and pencil records are stored in a locked room in a locked cabinet. All data will be checked for range and missing values.

### Statistical methods

Sociodemographics, scale scores, self-assessed outcomes, Fitbit data, and DLMO timepoints, will be described by summary and frequency statistics. Comparisons between groups will use parametric or non-parametric analyses according to normality distribution of data. Self-assessed daily data (depression, activity, and sleep) will be analyzed within a Mixed Model Repeated Measures analysis with a Random-effects Regression Model (RRM) [60]. Hamilton scale scores will be analyzed in a general linear model with baseline control. No interim analyses are planned.

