#### Psychometrics and sociodemographics

Sociodemographic data are collected at baseline together with a treatment outcome expectancy rating. Psychometric assessments are performed at baseline and at the endpoint visit. Rating window is set as last 3 days for all instruments except for the Pittsburgh Sleep Quality Index (PSQI) that covers the last month. The severity of depression is assessed by the Hamilton Depression Rating scale, 17 item version, which includes the core symptoms of depression (HAM-D_6_), and the Bech-Rafaelsen Melancholia Rating Scale (MES) focusing more on the cognitive symptoms of depression [50, 51]. The Hamilton rater is blinded to treatment allocation and is trained in the use of the HAM-D_17_ by repeated groups ratings with co-researchers. Self-assessed depression severity is measured by the Major Depression Inventory (MDI), a 10-item questionnaire covering both the ICD-10 and the DSM-IV diagnostic criteria for depression [52]. The response categories of each item are from “at no time” (0) to “all the time” [5], with a score range from 0 (zero) to 50 and a cut-off score of 21 for mild depression, 26 for moderate depression and 31 for severe depression. The WHO-5 Wellbeing index is used as a measure of Quality of life [53]. The WHO-5 consist of 5 items, each rated from “all of the time” (5) to “at no time” (0). The raw score is calculated by summing items multiplicated by four, giving a score range from 0 to 100, where 0 is worst possible and 100 is the best possible quality of life. The Morningness-Eveningness Questionnaire (MEQ) is a 19 items self-assessed questionnaire constructed to assess chronotype. A score below 42 indicates “evening type” and a score above 58 indicates “morning type”; and a score between 42 and 58 indicates “intermediate type” [54]. Sleep quality is assessed by the PSQI containing 11 self-reported items. These items are transformed into 7 “component scores” , and a “global score”. The components scores are “Subjective sleep quality (1)”, “Sleep latency (2)”, “Sleep duration (3)”, “Sleep efficiency (4)”, “Sleep disturbances (5)”, “Sleep medication (6)” and “Daytime dysfunction (7)”. A “Global Score” of 5 or above indicates poor sleep quality [55]. The System Usability Score (SUS) is used to evaluate the usability of the MDB system [56].

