#### Biochemical assessments

The Dim Light Melatonin Onset (DLMO) will be determined by saliva sampling every 45 min in the evening from 5 h before expected bedtime until 1 h after expected bedtime at baseline and endpoint (6 samples at each assessment day). The patient will collect samples at home according to a delivered 1-page guideline. The important rule from this guideline is to wear orange goggles (provided by investigators) for the entire 6-h episode of saliva sampling (to prevent suppression of melatonin secretion by blue light). The samples will be refrigerated and kept frozen until the melatonin assay. All samples obtained from a single patient will be assayed in the same batch to avoid inter-assay variability. The DLMO, a marker of circadian phase, is determined as the time point where melatonin production rises [57] using the hockey-stick method [58]. Patient-reported sleep data is used to calculate sleep midpoint. From sleep midpoint and DLMO, we can calculate the Phase Angle Difference (PAD) as a measure of entrainment [59]. The normal value of PAD is 6 h [56]. We expect patients to have a phase delayed DLMO relative to sleep midpoint with a PAD of approximately 5 h.

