### Ranking of outcomes

The primary outcome is the change in interviewer rated levels of depression (blinded) measured by the Hamilton Depression Rating scale 17-item version. The secondary outcome is the change in self-assessed depression level based on the scores on the Major Depressive Inventory. The tertiary outcome is the change, in minutes, of the Phase Angle Difference (PAD) on the subset of patients assessed with Dim Light Melatonin Onset (DLMO).

Explorative outcomes are: (a) changes in quality of life based on changes on the WHO-5 wellbeing scale, (b) self-rated depression severity from the MDB system (c) self-rated sleep quality from the MDB system, (d) chronotype from the MEQ and, (e) sleep quality assessed by the Pittsburgh Sleep Quality Index, (f) Fitbit pulse and activity data.

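### As written, MDI and PAD would be compared by a test chosen on normality and without a baseline covariate, forgoing precision that the plan takes for the Hamilton score

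*Protocol article*

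**What the plan says.** The Statistical methods section of the protocol article gives one general rule and two specific ones.

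- General: "Comparisons between groups will use parametric or non-parametric analyses according to normality distribution of data".
- Daily data: "Self-assessed daily data (depression, activity, and sleep) will be analyzed within a Mixed Model Repeated Measures analysis".
- Primary outcome: "Hamilton scale scores will be analyzed in a general linear model with baseline control".

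Ranking of outcomes then defines the next two outcomes as changes: "The secondary outcome is the change in self-assessed depression level based on the scores on the Major Depressive Inventory", and "The tertiary outcome is the change, in minutes, of the Phase Angle Difference (PAD) on the subset of patients" who have melatonin onset measured. Both have a baseline value. For the scales, "Psychometric assessments are performed at baseline and at the endpoint visit"; Biochemical assessments schedules saliva sampling at the same two time points.

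MDI and PAD are neither Hamilton scores nor daily self-ratings, so of the three rules only the general one can apply to them. The same holds for WHO-5, PSQI and MEQ.

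**The concern.** Two features of the general rule are weak for outcomes that are ranked and separately powered.

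First, the data choose the method. A parametric comparison estimates a mean difference; a rank test addresses a shift in distribution. The Sample size section powers MDI on a difference in mean points and PAD on a difference in mean minutes. If the data look non-normal, the analysis may answer a different question from the one that was powered.

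Second, no baseline covariate is named. MDI is a depression scale taken at the same two visits as the Hamilton scale, and the article gives no reason for handling it differently. When the arms have equal expected baselines, adjusting for baseline is more precise than comparing either endpoints or changes, for any baseline–endpoint correlation strictly between 0 and 1.

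At stake is the precision of the secondary and tertiary comparisons. The primary analysis is not affected.

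**Working it through.** **Inputs (Sample size and Design sections).**

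- MDI: mean 27 at baseline, falling to 22 (Standard) or 16 (CRT). Difference 22 − 16 = 6 points, SD 12, N = 128, so 64 per arm.
- PAD: CRT arm 5 h to 6 h, a change of 60 min; Standard arm 6 h unchanged. Difference in change 60 min, SD 80 min, N = 58, so 29 per arm.
- Both: alpha 0.05, power 0.80, 1:1 allocation.

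**Assumptions not in the article.** Tests are two-sided. The baseline–endpoint correlation r is not given; 0.3 to 0.7 is used. The article does not say whether each SD is of the endpoint or of the change, so both readings are shown. Baseline and endpoint SDs are taken as equal.

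**Step 1: reproduce the plan's figures.** For an unadjusted two-sample t-test the noncentrality is difference / (SD × √(2/n)).

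- MDI: 6 / (12 × √(2/64)) = 2.83, power 0.801. The smallest total N for 80% is 128, as stated.
- PAD: 60 / (80 × √(2/29)) = 2.86, power 0.801. The smallest total N is 58, as stated.

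The planned sizes therefore match a comparison without a covariate.

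**Step 2: SD under each analysis.**

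- Stated SD is of the endpoint: change score SD × √(2(1 − r)); baseline-adjusted SD × √(1 − r²).
- Stated SD is of the change: change score SD; baseline-adjusted SD × √((1 + r)/2), the ratio of the two expressions above.

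For MDI at r = 0.3, endpoint reading: change 12 × √1.4 = 14.2; adjusted 12 × √0.91 = 11.4.

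**Step 3: power at the planned N for MDI.**

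| Reading of SD | Analysis | r = 0.3 | r = 0.5 | r = 0.7 |
|---|---|---|---|---|
| Endpoint | Change score, unadjusted | 0.66 | 0.80 | 0.95 |
| Endpoint | Baseline-adjusted | 0.84 | 0.90 | 0.98 |
| Change | Change score, unadjusted | 0.80 | 0.80 | 0.80 |
| Change | Baseline-adjusted | 0.94 | 0.90 | 0.86 |

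The total N for 80% power with adjustment is 118, 98 and 68 on the endpoint reading and 84, 98 and 110 on the change reading. A simulation of the endpoint reading (4,000 runs per cell) gave 0.84, 0.90 and 0.97 adjusted and 0.67, 0.80 and 0.96 for change, in agreement.

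**Step 4: PAD.** With equal expected baselines the powers are the same to two decimals, because the standardized effect and N give the same 0.801 in Step 1.

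The planning means do not have equal baselines: CRT starts at 5 h, Standard at 6 h, and both end at 6 h. Taken literally, the endpoint difference is 0 and the adjusted difference is about 60 × r, that is 18, 30 and 42 min. Simulated power (SD 80 min at each visit) is then 0.13, 0.31 and 0.72 with adjustment, against 0.66, 0.80 and 0.95 for the change score. So the gain for PAD depends on equal expected baselines, which randomization implies and the planning inputs contradict. Biochemical assessments also expects about 5 h for patients in general, which does not fit a Standard arm at 6 h.

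**The case against.** The strongest reply is that the absence of adjustment is read from silence. MDI and PAD are not named in Statistical methods, a linear model with a covariate is itself a parametric analysis, and a separate analysis plan may specify it. This stands in part: nothing in the article excludes a covariate. But the article states a general rule and names baseline adjustment for the Hamilton score alone, so an unadjusted comparison is the natural reading, and the normality-driven choice is stated outright.

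Several stronger readings are tempting and are not supported:

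- *The baselines go unused.* Both outcomes are changes, so baseline enters by subtraction. What is missing is a baseline covariate.
- *The secondary and tertiary analyses are underpowered.* The stated sizes give 80% without adjustment if the SDs are of the change. The figure of 0.66 needs the endpoint reading and r = 0.3.
- *The comparison is biased by regression to the mean.* Under randomization this affects both arms alike, and the unadjusted difference in change is unbiased.
- *A rank test yields no estimate in points or minutes.* The Hodges–Lehmann shift is in those units, although it need not equal the mean difference that was powered.
- *The error rate is inflated by pre-testing.* The article does not specify a formal normality test, and no such effect has been quantified.
- *Normality is irrelevant here.* With 29 per arm, skew or outliers in PAD can matter. That is a reason for robust intervals and a sensitivity analysis.

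**Conclusion.** The point holds as a forgone gain in precision, together with a choice of method that should be fixed in advance. It is not an error that invalidates either outcome.

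For MDI the gain in power at the planned N is about 18, 10 and 2 percentage points at r = 0.3, 0.5 and 0.7 if the SD is of the endpoint (0.837 − 0.660, 0.900 − 0.801, 0.976 − 0.952). It is about 14, 10 and 6 points if the SD is of the change (0.936, 0.900 and 0.861, each less 0.801). The direction is the same on both readings. The size rests on an unstated correlation and an unstated meaning of the SD. On the endpoint reading the change-score test falls below the planned 80% when r is under 0.5.

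For PAD the same gains are conditional on equal expected baselines, and no firm figure can be given until the planning inputs are reconciled.

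**What to change.** In Statistical methods, replace the normality-based choice for MDI, PAD and the other scales taken at baseline and endpoint (WHO-5, PSQI, MEQ) with the model used for the Hamilton score: a linear model of the endpoint value on arm and baseline value, reporting the adjusted mean difference with its 95% CI. If residuals are clearly non-normal, keep that estimate and use robust or bootstrap intervals. Any rank-based test becomes a sensitivity analysis.

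In Sample size, reconcile the PAD baseline means of the two arms with randomization and with the expectation in Biochemical assessments, and state whether each SD is of the endpoint or of the change.

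The cost is a sentence or two and no new data. The change should be made before outcomes are examined by arm. If a separate analysis plan already names this model, only the published wording needs to be aligned with it.

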## Methods (monitoring)

### Data monitoring and auditing

According to Danish law, only drug trials are required to comply with Good Clinical Practice guidelines. Data analyses will be supervised by a trained statistician. The project is subject to auditing from the regional ethical committee.

### Harm

We do not expect that the study will expose any participants to serious adverse advents or reactions as their usual clinical management is maintained. All adverse events will be recorded and rules for reporting of serious adverse events and serious adverse reactions will be adhered to. Any harm due to the study procedures is covered by the Danish Patient Compensation Association.

## Ethics and dissemination

### Research ethics approval

The study was approved by The Regional Committee on Health Research Ethics (H-15013943) and the Danish Data Protection Agency (2012–58-004/ RHP-20016-0016). All participants will provide a signed informed consent before enrollment into the study. Informed consent will be obtained by the primary investigator. The project will be stopped if participants develop serious side effects or if the MDB system becomes unavailable. Patients can leave the study at any time at their own discretion.

### Consent or assent

The staff at the inpatient ward, or at the IOS, will ask the referred patient whether to consent to an information meeting about the study. The patient will receive written and oral information regarding the trial from an investigator. The patient will be asked to decide on participation within 2 days. If the patient accepts, the informed consent will be signed, and the inclusion and baseline assessments will begin.

### Confidentiality

Patient confidentiality will be secured by anonymous participant identification on all pen-and-paper sheets and in electronic files. The participant identification list is stored on a secure, password protected server, only accessible to investigators. MDB data are stored on a secure logged server where all data is secured by a unique identifier with data entry logs and edit trail.

### Access to data

The final data set will be accessible to all persons in the project group. Data analyses will be supervised by a qualified statistician.

### Dissemination policy

Results will be communicated as papers in peer-reviewed international journals, as posters, and as oral presentations at international symposia. All data whether negative, positive or inconclusive will be reported in full. All members of the project group are co-authors with a pre-arranged order. No professional writers will be used. Depending on the journal of publication, part of the protocol, statistical code, and dataset will be publicly available.

## Discussion

In the review by Van’t Hof from 2009, several advantages and disadvantages for electronic self-help interventions [61] are listed. These include: saving therapist time, letting the patients work at their own pace in their own home, avoiding social stigma by attending psychiatric services, can function as a first step to enter treatment, securing the anonymity of the patient, monitoring patient progress more closely. A number of disadvantages are listed including: the inability of self-help programs to take care of comorbidity, the clinical information based on non-verbal and verbal clues are lost, systems do not allow a proper diagnostic interview making misclassification and wrong treatment a risk, lack of response to complications during treatment unless the system includes clinician feedback, and some patients might not be able to handle electronic systems.

Our own experience with these systems, when used as a tool in depressed patients in an inpatient ward, is quite similar [6]. Electronic self-monitoring can give flexibility for patients that can use the programs whenever it suits them, patients can use the electronic self-monitoring system to prepare for a consultation with a psychiatrist, and progress or worsening can be co-monitored by patient and clinician and adequate steps can be taken earlier. Disadvantages are lack of face-to-face interactions, the risk of missing important symptoms that are not monitored, nonverbal communication between patient and psychiatrist is missing, no assessment of psychomotor inhibition and mood reactivity and some patients find it difficult to handle the electronic systems which can increase feelings of worthlessness.

The design of this trial is not a standard RCT with placebo control, but rather usual care with two different add-on treatments: electronic monitoring in the *Standard group* and electronic monitoring and Circadian Reinforcement Therapy in the *CRT group*. Participants might gain from participating in both treatment groups from using the MDB system that enables them to gain insight into their symptoms making some sort of empowerment likely. This might limit the possibility to show any superiority of the *CRT* method in these patients with more severe depression, where improvement is very slow. The effect of the *CRT* method has not previously been tested, and we cannot be certain that the CRT intervention will aid patients in the transition phase from inpatient to outpatient status. We have concerns whether patients in this phase are too burdened by depression symptoms to be able to integrate new knowledge and habits into their daily lives. Regarding the electronic monitoring system, our experience is that any procedure in this phase needs to be very user-friendly and adaptable. We have designed the MDB system to comply with these conditions, but we cannot know to what extent these patients can manage to self-assess their state and look at the graphical interface to deduce patterns and make changes to their daily activities and sleep habits.It is a limitation of the trial that we only include patients having been admitted to an inpatient ward. The reduces generalizability, as we cannot know whether patients with less severe depression might react differently to the intervention. It is also a limitation that the trial only covers a period of 4 weeks. Finally, the technology has already advanced since the design of the MDB system and currently, the direction is towards app-based systems that can be used directly on Smartphones.

We hope that the *CRT* in combination with the MDB system will prove to be an efficacious new non-pharmacological treatment for patients with depression building on empowerment by giving patients new monitoring tools, physiological and psychological insights, the opportunity to be more involved in their own treatment, and more access to clinicians. If the *CRT* intervention proves successful it might be used for longer durations to give more a sustained impact.

## Abbreviations

CRT: Circadian Reinforcement Therapy
DLMO: Dim Light Melatonin Onset
DSM-IV: Diagnostic and Statistical Manuals of Mental Disorders
HAM-D_17_: Hamilton Depression Rating Scale 17 item version
ICD-10: International Classification of Diseases 10th revision
IOS: Intensive Outpatient Service
M.I.N.I.: Mini International Neuropsychiatric Interview
MDB: Monsenso Daybuilder System
MEQ: Morningness-Eveningness Questionaire
MES: Bech-Rafaelsen Melancholia Scale
PAD: Phase Angle Difference
PSQI: Pittsburgh Sleep Quality Index
RCT: Randomized controlled trial
SCN: Suprachiasmatic nuclei of the hypothalamus
